#### Secondary outcomes

For secondary outcomes, including implementation outcomes (fidelity, appropriateness, sustainability) and patient-centeredness, we will use a combination of qualitative and quantitative methods. Descriptive statistics will summarize categorical variables as frequencies and percentages and continuous variables as means with standard deviations or medians with interquartile ranges. Fidelity to the interventions will be assessed by measuring RGM adherence (data uploads and blood glucose entries in Glooko), DSMT attendance rates, and CHW engagement (completion rates of initial education sessions, SDoH screeners, and follow-up meetings). Logistic regression will identify predictors of adherence.

Appropriateness and sustainability will be evaluated through qualitative analysis of focus group and interview data, which will be transcribed, coded, and analyzed thematically. Quantitative analyses will compare scores from validated surveys (Short Form-Diabetes Empowerment Scale (SF-DES) and Problem Areas in Diabetes (PAID)) between groups using paired *t*-tests or Wilcoxon signed-rank tests for within-group comparisons and independent *t*-tests or Mann–Whitney *U* tests for between-group comparisons.

In our secondary analysis, patients in treatment scenarios D or F will complete the DES-SF and PAID at 6 and 12 months, with scores compared between treatment scenario groups using a paired *t*-test or paired Wilcoxon test. For exploratory analysis, we will follow the same process, though our focus will be on assessing trends in both primary and secondary outcomes due to potential limitations in statistical power from the addition of the CHW enhancement.

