Sustainability	Short Form-Diabetes Empowerment Scale (SF-DES)	Change from baseline	Mean	6 and 12 months post enrollment	RedCAP Study Database
	Problem Areas in Diabetes (PAID) Survey	Change from baseline	Mean	6 and 12 months post enrollment	RedCAP Study Database
Patient-Centeredness	Respect for patients’ values, preferences, and expressed needs Coordinated and integrated Provide Information, communication, and education Ensure physical comfort Provide emotional support Involve family and friends	Qualitative self-reported experiences	N/A	Between 3 and 6 months after enrollment or rerandomization^a^	Patient Focus Group Discussions
Covariates	Race/ethnicity, Age, Sex, Zip code, Insurance status	Value	Distribution across categories	Baseline	EMR RedCAP Study Database

*RGM* remote glucose monitoring, *DSMT* diabetes self-management training, *CHW* community health worker, *EMR* electronic medical record, *SDOH* social determinants of health, *N/A* not applicable, qualitative measure

^a^Depending on initial and/or secondary if participant was assigned to RGM at their initial or rerandomization point

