### Sample size {14}

The sample size calculation, performed using G*Power (version 3.1), is based on the primary outcome of HbA1c over the 12-month study period, with the primary predictor being the six treatment conditions taken over the course of the study. The Null (H0) and Alternative (H1) Hypotheses are H0: There is no difference in the mean change in HbA1c among the six treatment groups, and H1: There is a significant difference in the mean change in HbA1c among the six treatment groups. The analysis assumes a significance level of 5%, 80% power, six treatment groups, equal group allocation, and a medium effect size of *f* = 0.25. The effect size of *f* = 0.25 was selected based on Cohen’s conventions for effect sizes in behavioral sciences, where 0.10 represents a small effect, 0.25 represents a medium effect, and 0.40 represents a large effect. A medium effect size is considered appropriate for this study, as it balances the detection of meaningful clinical differences with practical sample size considerations. Previous studies on diabetes management interventions such as DSMT and RGM have reported effect sizes in this range, indicating that a medium effect size is a reasonable expectation for interventions aimed at reducing HbA1c [13, 25].

The sample size estimation properly accounted for the multiple groups and comparisons inherent in the SMART design. Specifically, we conducted the sample size estimation for detecting a difference in HbA1c change across the six treatment groups, using an ANOVA framework, which inherently accounts for multiple comparisons. To ensure robustness and accommodate potential dropouts, we inflated the sample size by 20%. Thus, the minimum required sample size is 216 patients, and to account for an anticipated dropout rate, we aim to recruit 270 patients. This approach ensures that the study is adequately powered to detect significant differences across all treatment conditions, providing a solid basis for our subsequent analyses.

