#### Primary outcomes

To optimize the adaptive intervention and understand the causal effects of each proposed sequence, we will employ a SMART design. This design is particularly advantageous for chronic diseases like diabetes, where there is significant heterogeneity in response to treatment. The SMART design allows for re-randomization based on a tailoring variable, which in our study is the change in HbA1c at 6 months, enabling patients to receive an adaptive intervention that is most suited to their needs. To address potential imbalances in randomization, we will use stratified and block randomization techniques.

For primary analysis, we will employ linear regression models adjusting for baseline characteristics utilizing type III sum of squares to account for these discrepancies. Sensitivity analyses will include inverse probability weighting to account for any imbalances. To assess the overall HbA1c reduction by treatment condition and the average patient percentage point reduction in HbA1c from baseline to 12 months within each of the six treatment conditions, we will utilize one-way ANOVA for mean comparisons, followed by pairwise comparisons with a Tukey post hoc test to correct for multiple comparisons. In cases of non-normal data distribution, we will opt for Kruskall-Wallis tests and a Dunn post hoc test with Hommel multiple comparison *p*-value corrections.

Linear regression will be employed to adjust for additional covariates that may confound the relationship between treatment and outcome, such as baseline characteristics with residual confounding post-randomization, and baseline and 6-month HbA1c values. We will also test for possible interactions of covariates with the treatment variable, reporting model adjusted slopes (β_ADJ_), 95% confidence intervals, model diagnostics, and goodness of fit (via R^2^).

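### SF-DES and PAID are compared by two-group tests in a six-condition trial, without the baseline score as a covariate, over a family of comparisons the text does not fix and with a mixed secondary and exploratory status

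*Protocol article*

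**What the plan says.** All places are in the protocol article.

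- **Statistical methods {20a}, Secondary outcomes.** The survey scores are compared by paired tests within groups and by "independent *t*-tests or Mann–Whitney *U* tests for between-group comparisons". The groups are not named. The next paragraph mentions only scenarios D and F, and describes a paired test between scenario groups. A closing sentence limits the exploratory analysis to trends because power may be limited.
- **Outcomes {12}, Table 2.** Under Sustainability, each scale has the entry "Change from baseline Mean 6 and 12 months post enrollment". The baseline score is therefore collected and is used through a change score.
- **Statistical methods {20a}, Primary outcomes.** For HbA1c across the six conditions the plan is one-way ANOVA, "followed by pairwise comparisons with a Tukey post hoc test to correct for multiple comparisons", or Kruskal-Wallis with Dunn and Hommel if the data are not normal.
- **Status of sustainability.** Outcomes {12} and the Secondary outcomes section treat it as secondary. The Abstract and Objectives {7} (Exploratory Aim 3a) treat it as exploratory.
- **Sample size {14}.** "The analysis assumes a significance level of 5%, 80% power, six treatment groups, equal group allocation, and a medium effect size of" 0.25. This applies to HbA1c. No separate significance level is given for the surveys.

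**The concern.** A two-sample test can cover six conditions only by being repeated. For HbA1c the plan recognises this and uses an overall test with corrected pairwise comparisons. For the surveys, on the same patients, it prints a different procedure that has neither. The number of contrasts, the leading time point and the inferential status are all open, so a nominal p-value below 0.05 between two paths on one scale could be read as evidence that one sequence sustains self-management better, when it is one of several chances for such a result.

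There is also an efficiency issue that does not depend on multiplicity. A baseline score is in hand, and a change-score or raw-score two-sample test uses it less well than a model with that score as a covariate.

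**Working it through.** **1. The plan's own figure.** Inputs from Sample size {14}: alpha 0.05, power 80%, six groups, f = 0.25. Noncentral F with lambda = N x f^2 and 5 and N - 6 degrees of freedom.

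- The smallest N is 211 (lambda = 211 x 0.0625 = 13.19, power 80.0%).
- Rounded up to six equal groups, N is 216 (lambda = 13.5, power 81.1%).
- Allowing for 20% dropout, 216 / 0.8 = 270.

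Both stated figures reproduce, and 216 / 6 = 36 per path under "equal group allocation".

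**2. Size of the family.** Six paths give 6 x 5 / 2 = 15 pairs. Two scales at 12 months give up to 30 tests. A single contrast gives 2 tests at one time point or 4 at two.

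**3. Chance of at least one false positive.** For m independent tests at 5% this is 1 - 0.95^m:

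- m = 2: 9.75%
- m = 4: 18.5%
- m = 15: 53.7%
- m = 30: 78.5%

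The last two are too high, because pairs share groups and the scales are correlated. The correlated case was therefore simulated under no difference anywhere: 10,000 replicates, 36 per path (108 per first-stage arm), and two-sided pooled t-tests at 5%. Assumed inputs, not in the documents, are a between-scale correlation of 0 to 0.7 and a between-time correlation of 0.5.

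| Comparisons, both scales | One time point | Two time points |
|---|---|---|
| D against F | 9.0-9.8% | 15.0-17.5% |
| Two first-stage arms | 8.8-9.8% | 15.1-17.2% |
| Two re-randomised contrasts | 16.6-18.8% | 27.9-32.0% |
| Path E against the other five | 29.0-33.6% | 46.5-52.9% |
| All 15 pairs | 52.3-60.5% | not used (see below) |

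All 15 pairs on one scale at 12 months give 36-37%. At a between-scale correlation of 0.8 (4,000 replicates), all 15 pairs on both scales give 49.7%, which sets the lower end of the 50-61% range. Unequal paths (54, 27 and 27 in each arm) give 52.1-59.7%, so the equal-size assumption matters little. The all-pairs figure at two time points is not used: at 6 months only two first-stage assignments exist, so 15 randomised pairs cannot be counted there.

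**4. Precision.** Let r be the correlation between baseline and follow-up score, with equal variances at both times and a linear model. The variance of a group difference, relative to the raw follow-up score, is 1 for raw scores, 2(1 - r) for change scores and 1 - r^2 with baseline adjustment. The documents give no r.

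| r (assumed) | Raw | Change | Adjusted |
|---|---|---|---|
| 0.3 | 1.00 | 1.40 | 0.91 |
| 0.5 | 1.00 | 1.00 | 0.75 |
| 0.7 | 1.00 | 0.60 | 0.51 |

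Adjustment is never worse in this range. Against change scores the ratio is (1 + r)/2, that is 0.65, 0.75 and 0.85.

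**5. Which contrasts are randomised.** Whether a patient stays or is re-randomised depends on the 6-month HbA1c change (Trial design {8}). Responder and non-responder paths therefore differ by selection. A difference between them need not be a false positive, and it is not a treatment effect either. The randomised contrasts are the two first-stage arms and, within each arm, the two second-stage options among non-responders.

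**The case against.** The strongest reply is that this is a condensed article, and multiplicity rules for secondary scales are normally left to the analysis plan. That stands: the missing correction rule alone is no finding, and neither is the lack of such a rule for the sentence "Logistic regression will identify predictors of adherence". What remains is that the article does print a test for the surveys, and that test does not fit six conditions.

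A reader might infer that a false survey difference is more likely than not. The documents do not support that. It requires all 15 pairs on both scales, or several path contrasts on both scales at both time points, and no such family is written. The only paths named for these scores are D and F, which give about 9-18%.

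A reader might also infer that the surveys have no hierarchy or exploratory label. They have both: HbA1c is ranked primary and sustainability secondary, and the Abstract and Objectives {7} name sustainability as exploratory. The fault is that these labels disagree.

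Nor is baseline ignored, since Table 2 specifies change scores. The point is the weaker one of covariate adjustment.

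Finally, section {20c} mentions Q-learning, g-estimation, one-way ANOVA and linear regression for primary and secondary outcomes together. This shows that an overall test or regression is within the authors' intentions, but it does not assign either to the surveys. The only place that names the survey tests keeps the two-sample ones.

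**Conclusion.** The point holds in a limited form. The stated two-group tests do not fit a six-condition design, the family they generate is undefined, and the status of sustainability conflicts between sections. The resulting error rate is about 9-18% for one contrast on both scales and about 50-61% for all pairs on both scales at 12 months. The documents do not show which applies, so neither end should be quoted as the plan's error rate.

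These figures assume 5% two-sided per test, no true differences, paths of 36 and the assumed correlations. They do not cover selection differences between responder and non-responder paths.

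The precision gain from baseline adjustment (0.75 against 1.0 at r = 0.5) rests on an assumed r and a linear model. The primary HbA1c analysis is unaffected.

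**What to change.** In Secondary outcomes, replace the between-group two-sample tests with one linear model per scale: the 12-month score on randomised assignment, adjusted for the baseline score.

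- Take an overall test first, as a joint test of the randomised contrasts. A six-path comparison would mix in responder selection.
- Limit contrasts to the first-stage arms and, within each arm, the second-stage options among non-responders. That is three per scale and six in all. Either adjust them (Holm, or Tukey where several levels are compared; the first Holm step over six tests is 0.05 / 6 = 0.0083), or label them exploratory and report estimates with 95% confidence intervals.
- Name 12 months as the main time point and treat 6-month and within-group results as descriptive.
- State once whether sustainability is secondary or exploratory, and align the Abstract, Objectives {7}, Outcomes {12} and Secondary outcomes.
- Clarify the sentence on D and F. A paired test suits 6 against 12 months in the same patients, not one scenario against another.

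The cost is wording and a small amount of analysis work, with no new data. Single contrasts lose a little power after adjustment, partly offset by the precision gained from the baseline covariate.

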### Trial design {8}

This study uses a sequential, multiple assignment, randomized trial (SMART) design with approximately 270 Black/Latine patients living with diabetes recruited from two locations of a diabetes and endocrinology clinic (“the Center”) in Chicago, IL. A SMART is a type of adaptive trial that uses at least two points of randomization to build the evidence for an optimal intervention or treatment. In the IDEA study SMART, we will test three components of a team-based care model that provides diabetes care and management for patients living with diabetes and other complex health and social needs. HbA1c will serve as our pre-planned tailoring variable which will determine participant rerandomization. At 6 months, participants with an HbA1c of at least one percentage point improvement from their baseline measurement will be considered “responders”; participants with an HbA1c that has not improved by at least one percentage point from their baseline measurement will be considered “non-responders”. The study will be conducted by Sinai Urban Health Institute (SUHI), the community-engaged research institute within Sinai Chicago, a safety-net health system in Chicago, IL. See Fig. 2. IDEA Study SMART Design, for the study design. We hypothesize that path E (DSMT to CHW) will have the largest reduction in A1c compared to all other paths. DSMT provides actionable education and guidance for improving diabetes management, whereas RGM focuses on information tracking for both patients and providers. The CHW will reinforce information taught during DSMT sessions.

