### Eligibility criteria {10}

Eligibility criteria for each study component (SMART, participant focus group discussions, and staff interviews) are described in Table 1.

**Table 1 Tab1:** IDEA study eligibility criteria

Study component	Inclusion criteria	Exclusion criteria
SMART	• Diagnosed with type 1 or type 2 diabetes • 18 years of age or older • Able to provide informed consent • African American/Black or Latine • HbA1c level ≥ 7% measured within 365 days prior to study enrollment • Have a smartphone compatible with the Glooko RGM application [20] • Completed at least one appointment at the Center since the Center opened in 2020 • Fluent in English or Spanish	• Have an activated Power of Attorney • Diagnosed with Stage V renal disease or undergoing dialysis • Diagnosed with a severe form of cardiovascular disease • Diagnosed with gestational diabetes only (without type 1 or type 2) • Diagnosed with any severe form of mental disorder including schizophrenia, bipolar disorder, or severe depression • Pregnant • Diagnosed with Alzheimer’s disease or dementia • Already an active user of RGM • Actively working with a CHW for their diabetes • Planning to travel outside of the Chicagoland area for more than three months in the year following study enrollment • Use a continuous glucose monitor that is incompatible with the Glooko RGM application
Participant Focus Group Discussions	• Meet all eligibility for SMART component of study • Completed at least 3 months of their assigned SMART study condition	None
Center Staff Interviews	• Employed by the Center during the study period • 18 years of age or older • Able to provide informed consent • Fluent in English or Spanish	None

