### Methods for additional analyses (e.g., subgroup analyses) {20b}

In our additional analyses, we aim to explore the potential moderating effects of various demographic and socioeconomic factors on the effectiveness of our stepped-care TBC intervention. Specifically, we will conduct subgroup analyses to investigate whether the impact of the intervention varies across different levels of Race/ethnicity, Age, Sex, and Insurance status. We will employ interaction terms in our regression models to test for statistical interactions between the treatment conditions and these covariates. This will help us to identify any differential effects of the intervention across various subgroups, providing insights into the equity of our intervention and highlighting any potential disparities in its effectiveness. For instance, we will include interaction terms between the treatment conditions and Race/ethnicity to assess whether the intervention’s impact on HbA1c reduction differs between Black/Latine patients and other racial/ethnic groups. Similarly, we will investigate potential age and sex interactions to explore whether the intervention is more or less effective in older versus younger patients, and in male versus female patients.

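### A paired test is named for comparing different patients in scenarios D and F, and the example race/ethnicity contrast uses a comparator that the trial does not enrol

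*Protocol article*

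**What the plan says.** **Scale comparison.** In the protocol article, Statistical methods {20a}, Secondary outcomes, the last paragraph says that "patients in treatment scenarios D or F will complete the DES-SF and PAID at 6 and 12 months". The test it names is of the paired kind, either the t-test or its Wilcoxon counterpart, and the comparison to which it applies is described in these words: "with scores compared between treatment scenario groups using a paired". The paragraph before it covers the same two scales. It gives paired t-tests or Wilcoxon signed-rank tests to within-group comparisons, and independent t-tests or Mann–Whitney U "tests for between-group comparisons".

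**Status of D and F.** Sample size {14} states the null hypothesis as "There is no difference in the mean change in HbA1c among the six treatment groups". Primary outcomes in {20a} compares the six conditions by one-way ANOVA, so the plan itself treats them as separate, independent groups.

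**Race/ethnicity.** Methods for additional analyses {20b} plans interaction terms between treatment and several covariates. Its worked example asks whether the "impact on HbA1c reduction differs between Black/Latine patients and other racial/ethnic groups". Table 1 under Eligibility criteria {10} lists "African American/Black or Latine" as an inclusion criterion for the SMART component, and Trial design {8} describes about 270 Black/Latine patients.

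**The concern.** A paired test needs a link between each observation in one group and one observation in the other. Two measurements on the same patient give that link; two sets of unmatched patients do not. Read literally, the D/F sentence asks for a test with no defined pairs. It also leaves the plan with two incompatible tests for one between-group comparison of empowerment and distress scores, so the choice stays open until the data are in.

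The example in {20b} has a different fault with a similar result. It names a comparator that the eligibility criteria exclude, so an analyst who follows it has nothing to estimate. In a trial designed around equity, a reader will look for the race/ethnicity interaction, and the one contrast spelled out for it is empty.

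**Working it through.** **1. The plan's own figures.** Inputs from Sample size {14}: six equal groups, f = 0.25, two-sided 5% level for the omnibus F test, 80% power, 20% dropout. With a noncentral F distribution, noncentrality f² × N and degrees of freedom 5 and N − 6, the smallest N that reaches 80% power is 211. Rounded up to six equal groups this is 216 (power 0.811), or 216/6 = 36 per group. Allowing for dropout, 216/(1 − 0.20) = 270. Both figures reproduce. Neither uses the two sentences at issue.

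**2. Paired test, unequal groups.** A paired test works on the differences dᵢ = xᵢ − yᵢ, i = 1, …, n, and so needs the same n on both sides. Nothing in the design makes D and F equal in size after dropout. With, say, 30 and 36 patients, the paired t-test routine returns an error and no result.

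**3. Paired test, equal groups.** With 36 patients on each side the routine returns a number, but the number depends on which patient is set against which. Two illustrations on simulated data, each re-paired at random 5,000 times:

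| Simulated data set | Independent-samples p | Paired p, lowest to highest |
|---|---|---|
| A: observed difference 0.45 SD | 0.060 | 0.007 to 0.148 (median 0.065) |
| B: drawn with a true difference of 0.5 SD | 0.19 | 0.058 to 0.296 |

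Data set A can be checked by hand: t = 0.45 × √(36/2) = 1.91 on 36 + 36 − 2 = 70 degrees of freedom, p = 0.060. The paired version has 36 − 1 = 35 degrees of freedom. The size of the difference in both data sets is an assumption; the documents give no expected difference for either scale. The table shows only that one data set has one independent-samples p-value and many paired ones.

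**4. Internal contradiction.** The two paragraphs of Secondary outcomes, side by side:

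| Comparison of DES-SF and PAID scores | Earlier paragraph | Last paragraph |
|---|---|---|
| Within a group | paired | not separately stated |
| Between groups | independent | paired |

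**5. Race/ethnicity example.** Write the model with 6 treatment columns, 1 race indicator (other versus Black/Latine) and 5 products: 6 + 1 + 5 = 12 columns. Every enrolled patient is Black or Latine, so the indicator and all 5 products are zero throughout. The rank is 6, and the race effect and every interaction are not estimable. With the indicator redefined as Black versus Latine, and both groups present in all six conditions, the rank was the full 12 in a simulated sample of 216.

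**The case against.** The strongest reply on the scales is that the right rule is already in the text. The preceding paragraph separates paired from independent tests correctly, and the D/F sentence mentions 6 and 12 months, so it may be a garbled account of change within each scenario. That reading is plausible and would be valid. It is not what the sentence says, however, and the sentence needs rewording on either reading.

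A second reply is that the paired test is not wrong in the sense of inflating error. This stands in part. If the groups are equal in size and the pairing ignores the data, the differences are independent and identically distributed, and the test keeps its nominal level. What remains is arbitrariness, lost degrees of freedom (35 against 70), and no result at all with unequal groups. The p-value ranges above are therefore illustrations and do not measure bias in this trial.

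A reader might infer two further faults that the documents do not support:

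- **That only D and F patients complete the scales.** The sentence does not say only. The abstract and Table 2 apply the scales without restriction.
- **That a D/F comparison wrongly omits a CHW path.** Trial design {8} does label DSMT followed by CHW as path E, and Exploratory Aim 3a concerns CHW support. But the D/F sentence is introduced as a secondary analysis, with exploratory analysis taken up in the next sentence. Fig. 2, which defines the letters, is not available here. No error can be shown; the letters merely deserve a check.

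On race/ethnicity, the contrast is introduced as an instance, under additional analyses. The general plan of treatment-by-race/ethnicity interaction terms can be estimated within the enrolled population. That objection stands, and it limits the point to the example.

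**Conclusion.** Both sentences are wrong as written. The D/F sentence assigns a paired test to unmatched patients: it is uncomputable with unequal groups, arbitrary with equal ones, and at odds with the plan's own rule one paragraph earlier. The {20b} example has zero eligible participants on one side.

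The reach is limited. The first affects a secondary analysis of DES-SF and PAID; the second affects one worked example, and the wider interaction plan can stand. The primary HbA1c comparison, the 216 and the 270 are untouched. The conclusion assumes only that D and F are distinct conditions with different patients, which the six-group ANOVA implies, and that Table 1 is applied as written. It does not depend on what D and F contain.

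**What to change.** - **Secondary outcomes, last paragraph.** Replace the paired test between scenarios with an independent-samples comparison of D and F, in line with the preceding paragraph. Preferably make it a linear regression of the 12-month score on scenario, adjusted for the earlier score, and name in advance which earlier score is meant. Keep paired tests for change from 6 to 12 months within a scenario. The independent test is a change of wording; the regression adds a little analysis work.
- **Scenario letters.** Check D and F against Fig. 2, path E and Exploratory Aim 3a, and confirm that the intended scenarios are named. This is a check, with an edit only if the letters prove wrong.
- **{20b} example.** State the race/ethnicity contrast as Black versus Latine and leave the rest of the interaction plan as it is. Wording only.

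No change to data collection or sample size is needed.

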**Methods:**

Using implementation science and racial equity principles, this study aims to (1) evaluate the appropriateness; (2) measure fidelity; and (3) compare the effectiveness of varying the combination and sequence of three interventions. An exploratory aim will measure sustainability of intervention adherence and uptake. This mixed-methods trial employs a sequential, multiple assignment randomized trial (SMART) design, patient focus group discussions, and staff interviews. Eligible Black/Latine patients will be recruited using patient lists extracted from the electronic medical record system. After a detailed screening process, eligible patients will be invited to attend an in-person enrollment appointment. Informed consent will be obtained and patients will be randomized to either DSMT or RGM. At 6 months, patients will complete two assessments (diabetes empowerment and diabetes-related distress), and HbA1c values will be reviewed. “Responders” will be considered those who have an HbA1c that has improved by at least one percentage point. “Responders” remain in their first assigned study arm. “Nonresponders” will be randomized to either switch study arms or be paired with a CHW. At 6 months participants will complete two assessments again, and their HbA1c will be reviewed. Twelve patient focus groups, two for each intervention paths, will be conducted along with staff interviews.

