Randomization envelopes were created for the second round of randomization at 6 months following a similar protocol. In this case, the staff member printed 60 pieces of paper that say “CHW,” 60 pieces of paper that say “RGM,” 60 pieces of paper that said DSMT, and 60 pieces of paper that say “CHW + RGM.” We assumed that a certain number of participants would improve by at least one percentage point and would not be randomized. After creating the 240 envelopes, the staff member created two boxes of envelopes, stratified by the initial treatment assignment. In the first box, for participants initially assigned to DSMT, the staff member shuffled and placed the CHW and RGM envelopes in the box marked “DSMT.” In the second box, for participants initially assigned to RGM, the staff member shuffled and placed the remaining DSMT and CHW + RGM envelopes in the box marked “RGM.”

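### A paired test is named for comparing SF-DES and PAID scores between scenarios D and F, which contain different, unmatched patients

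*Protocol article*

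**What the plan says.** All three statements on testing are in the protocol article, Statistical methods {20a}, Secondary outcomes.

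- The second paragraph sets a general rule for SF-DES and PAID. Paired methods belong within a group: it names "Wilcoxon signed-rank tests for within-group comparisons and independent" ones, meaning the unpaired t-test and the Mann-Whitney U test, as "tests for between-group comparisons".
- The third paragraph turns to two named paths. Participants on D or F fill in both scales at the 6- and 12-month visits, "with scores compared between treatment scenario groups using a paired" version of either the t-test or the Wilcoxon test.
- The next sentence says that the exploratory analysis uses the same procedure, with attention to trends because power may be limited.

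How patients reach a path is stated elsewhere. In the Abstract (Methods), responders "remain in their first assigned study arm" and nonresponders "will be randomized to either switch study arms or be paired with a CHW". Under Sequence generation {16a}, the second randomization uses individual envelopes: "the staff member created two boxes of envelopes, stratified by the initial treatment assignment". No matching of participants is described.

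**The concern.** A paired test needs a defined partner for each observation. The only natural partner in this design is the same patient's score at another visit. That supports a comparison over time within a scenario, not a comparison of scenario D with scenario F. The sentence therefore names a test that does not fit the comparison it describes, and it conflicts with the rule one paragraph earlier for the same scales.

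An analyst who follows it literally must invent a pairing and, when the groups differ in size, discard patients. An analyst who reads it as a 6-to-12-month test within patients gets a legitimate description, but not the between-scenario result that the sentence announces. SF-DES and PAID are the two quantitative sustainability measures in Table 2, so the choice should not be left open.

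**Working it through.** **1. The plan's only sample-size figures.** Sample size {14} gives a one-way ANOVA with k = 6, f = 0.25, alpha = 0.05 and 80% power. With noncentrality N × f², the smallest N reaching 80% is 211 (power 0.800). Rounded up to six equal groups this is 216 (power 0.811). Dropout: 216 / (1 − 0.20) = 270. Both figures reproduce. They belong to HbA1c; none is stated for the SF-DES/PAID comparison.

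**2. Do pairs exist?** Responders stay on one path. Nonresponders draw one envelope and follow one path. No participant is on two of the six paths, and allocation is stratified only by first arm. Any two paths are therefore independent, unmatched samples. Fig. 2 is not available in the text, so the content of D and F cannot be confirmed, but this step does not depend on it.

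**3. Would the groups be equal in size?** Assume that D and F are nonresponder paths and that a fraction r responds (the article gives no rate).

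- Expected size per path = (N/2) × (1 − r)/2. With N = 216: 43.2 at r = 0.2 and 27.0 at r = 0.5. With N = 270: 54.0 and 33.75.
- If the two paths start from different first arms, take each size as Binomial(N/2, (1 − r)/2). The chance of equal sizes is the sum of squared probabilities: 0.057 (N = 216, r = 0.3), 0.063 (216, 0.5), 0.051 (270, 0.3) and 0.056 (270, 0.5).
- If they start from the same first arm, let K ~ Binomial(N/2, 1 − r) be its nonresponders, drawing without replacement from a box of 60 + 60 envelopes. The chance of equal sizes is the sum over even k of P(K = k) × C(60, k/2)² / C(120, k): 0.075, 0.073, 0.089 and 0.073 in the same order.

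The sizes therefore agree in roughly 5% to 9% of trials. Otherwise the paired test cannot be computed on all patients.

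**4. What if the sizes happen to agree?** Take 36 per group (216/6) as an illustration.

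- One simulated data set (normal scores, true difference 0.5 SD) had an independent t-test p of 0.039. Over 5,000 arbitrary pairings of the same data, the paired p ran from 0.002 to 0.10, with its central 95% from 0.015 to 0.075.
- With no true difference, 20,000 simulated trials rejected in 5.0% with random pairing and in 5.0% with the independent test.
- If the rows happened to be sorted by score before pairing, rejection rose to 69%.

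**5. The two paragraphs side by side.**

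| Comparison of SF-DES/PAID | Second paragraph | Third paragraph (D or F) |
|---|---|---|
| Within a group, over time | paired t / signed-rank | not described |
| Between groups | independent t / Mann-Whitney U | paired t / paired Wilcoxon |

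The lower row is a direct contradiction.

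**The case against.** The strongest reply is that this is loose wording. The correct rule stands one paragraph earlier, and the D/F sentence mentions repeated scores at 6 and 12 months, so the authors may have meant change within each scenario. That is plausible. It lowers the weight of the point but does not remove it, because the text names a comparison between scenario groups and an analyst cannot tell which of the two was intended.

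Three stronger readings might be inferred, and the documents do not support them.

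- *That the test inflates false positives.* With a pairing unrelated to the scores, average type I error stays near 5%, and power is almost that of the independent test (0.54 against 0.55 for a 0.5 SD difference, 36 per group). The 69% arises only if rows are paired after sorting on score, which the article does not propose.
- *That the community health worker question rests on this test.* Trial design {8} labels DSMT to CHW as path E, which is outside a D/F comparison, and Fig. 2 is not shown. The CHW enhancement enters only through the next sentence, on exploratory analyses. The link is indirect.
- *That the trial would rely on an uncontrolled before-after test.* On the within-patient reading, the independent between-group tests of the second paragraph still apply. How often a paired test would react to general drift alone depends on an assumed drift. With 36 patients and a 6-to-12-month correlation of 0.5 to 0.7, it is 9–12% at 0.1 SD, 21–33% at 0.2 SD and 42–62% at 0.3 SD. The article supports none of these values in particular.

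**Conclusion.** The sentence is wrong as written. It assigns a paired test to two independent groups and contradicts the rule for the same scales one paragraph earlier. Followed literally, it usually cannot be run without discarding patients, and when it can, its p-value depends on an arbitrary row order. The lack of pairs follows from the design and needs no assumption. The 5% to 9% chance of equal sizes assumes two nonresponder paths and 30% or 50% response, and the spread of p-values comes from one simulated data set with 36 per group.

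The effect is confined to a secondary analysis and to the exploratory analysis that copies its procedure. The primary HbA1c analysis and the figures 216 and 270 are untouched. It should be corrected before analysis, but it does not threaten the trial's main result.

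**What to change.** Rewrite the D/F sentence so that comparisons between scenario groups use the independent t-test or Mann-Whitney U test that the section already names, and state whether they are made on the 12-month score or on change. Keep the paired t-test or Wilcoxon signed-rank test only for the 6-to-12-month change within each scenario, and say that this change is not read as a difference between scenarios. The exploratory analysis is then corrected through its cross-reference.

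Optionally, analyse the 12-month score by ANCOVA with the 6-month score as covariate. Relative to a 6-to-12-month change score, the variance ratio is (1 − r²) / [2(1 − r)] = (1 + r)/2. This is 0.75 at r = 0.5 and 0.85 at r = 0.7, so 25% and 15% lower variance; these correlations are assumptions. It is a gain in precision, not needed to cure the error.

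The cost is wording only: no new data, no added visits and no change to the sample size.
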